### Recruitment and consent

#### RCs

We will contact REMAP-CAP site RCs by email and invite them to participate in this SWAT. RCs who consent to participate in this SWAT will screen patients for eligibility for the REMAP-CAP trial as usual and include the infographic as part of their standard verbal description of the REMAP-CAP trial. At the conclusion of each consent encounter, regardless of their decision to participate, the RC will inform the patient/SDM that our research team is working to improve the consent experience for future trial participants and invite them to participate in a follow-up survey.

#### Patient/SDM

REMAP-CAP requires written consent for study participation. All participants will receive the standard REMAP-CAP consent documents with a verbal description of the trial. Eligible patients, or their SDMs, who are approached for participation in REMAP-CAP with the infographic will automatically be eligible for this SWAT. At the conclusion of the REMAP-CAP consent discussion, patients or SDMs will be invited to participate in a follow-up survey. If the patient/SDM agrees to follow-up and can receive and complete an electronic survey, the RC will advise the patient/SDM that a member of the research team will send an email within 24 h to seek feedback on their consent experience. The RC will inform the patient/SDM that the decision to provide feedback will not impact quality of care and the RCs will not see their responses. The RC will provide the SWAT research team with the participant’s name and contact information by email or by phone. The follow-up email, sent centrally by the SWAT research team, will outline survey objectives, invite the individual to participate, and will contain an electronic survey link.

For patients/SDMs who are unable to receive or complete an electronic survey, we will provide the option to complete a paper version. If the patient/SDM agrees to follow-up, the RC will provide them with a paper copy in an unsealed envelope. These patients/SDMs will be asked to complete the paper survey within 1 week and return it to the ICU research office. Site RCs will be asked to scan and email completed surveys to the SWAT research team for central data entry.

At the beginning of the survey, we will inform potential respondents that their participation is voluntary, that completed questionnaires will remain confidential, and provide contact information where a member of the team can address any questions. For electronic questionnaires, we will send nonrespondents a reminder email 1 week after the initial email. Before recontacting patients and/or SDMs, the SWAT research team will communicate with site RCs to ensure it is an appropriate time for communication. Participant timeline and activities are summarized in Table 1.

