### Sample size

We will use a sample of consecutive REMAP-CAP consent encounters at each of our study sites. Due to funding and study personnel constraints, we will recruit patients/SDMs for up to 6 months. Based on historical recruitment rates, we anticipate 2 patients per month, per site, for a total of 60 patients/SDMs. We conducted a sample size calculation using a confidence interval approach and expect our target sample size of 60 patients/SDMs to be sufficient to achieve our feasibility objectives [30]. We selected eligible consent encounters as our most important outcome, thus basing our calculation on a proportion of ≥ 68%, alpha = 0.1 and a margin of error of 10%, for a sample size of 60. We will seek feedback from all RCs consenting during this time. We anticipate 1–2 RCs per site for a total of 5–10 RCs. We will meet with RCs at each site before study implementation.

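### The assurance that research coordinators will not see survey responses cannot be kept for paper surveys, which site coordinators scan and email

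*Protocol article*

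**What the plan says.** The relevant text is the Patient/SDM part of Recruitment and consent in the Phase 2 methods.

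- **Assurance.** After the REMAP-CAP consent discussion the RC invites the patient or SDM to a follow-up survey and says that "the decision to provide feedback will not impact quality of care and the RCs will not see their responses".
- **Electronic route.** The survey link is emailed centrally by the SWAT research team, so the answers do not pass through the site.
- **Paper route, who it is for.** "For patients/SDMs who are unable to receive or complete an electronic survey, we will provide the option to complete a paper version".
- **Paper route, hand-out.** If the person agrees to follow-up, "the RC will provide them with a paper copy in an unsealed envelope".
- **Paper route, return.** Respondents are asked to "complete the paper survey within 1 week and return it to the ICU research office".
- **Paper route, processing.** "Site RCs will be asked to scan and email completed surveys to the SWAT research team for central data entry".
- **Statement at the start of the survey.** Respondents are told that "completed questionnaires will remain confidential", with no distinction by mode.

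The Sample size section adds: "We anticipate 1–2 RCs per site for a total of 5–10 RCs".

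**The concern.** The plan treats keeping the answers from the RCs as worth promising, and the electronic route delivers it. The paper route does not: the staff whose encounter is being rated process the open answer pages. Two things are at stake.

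The first is the accuracy of what participants are told. Critically ill patients and their families would be given a statement that the written procedure makes untrue, in a study whose purpose is to improve consent.

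The second is the quality of the CUE-R 2 data. A respondent who knows or suspects that the RC will read the form may soften criticism or not return it. That would act on paper respondents only, and these are by design the people who cannot use the electronic survey.

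**Working it through.** No figure in the plan is in dispute, so the check is mainly a comparison of texts, followed by an indication of scale.

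**Step 1. Scope of the assurance.** The sentence comes after one about electronic surveys, but it carries no restriction to that mode. Its first half, on quality of care, plainly applies to everyone invited. No alternative wording is given for paper respondents.

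**Step 2. Who handles a completed paper form.** It goes from the respondent to the ICU research office, then to a site RC who scans and emails it, then to the SWAT team. A completed form cannot be scanned without its answer pages being open. No step in the text shields the answers. Steps 1 and 2 cannot both be carried out as written for a paper respondent.

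**Step 3. How close the scanner is to the encounter.** With one RC at a site, the scanner is the RC who ran the encounter. With two, it may be a colleague. The assurance refers to the RCs collectively, so it fails in both cases. The plan anticipates 2 patients per month per site for up to 6 months: 2 × 6 = 12 per site, and 12 × 5 sites = 60, which matches the stated total. Each form also ends with five demographic questions. With about 12 encounters per site, a form could often be linked to a person.

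**Step 4. Which CUE-R 2 items are plausibly sensitive (Table 2).**

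- Total 26, less 5 demographic = 21.
- Of these 21, 2 record consent mode and decision, which the RC already knows, and 4 test trial knowledge: 21 − 2 − 4 = 15.
- Of these 15, the items on satisfaction with information (1 + 2 = 3), acceptability of the infographic (1 + 3 = 4) and confidence in the decision (1) make 3 + 4 + 1 = 8. These are the most exposed.
- The rest concern use and ease of use of the infographic and the documents, and the wish for more information.

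**Step 5. Scale, on assumptions only.** The number of exposed forms is the paper share times the number of completed surveys. The plan gives neither. Two illustrations, taking the success thresholds in Data analysis as if just met:

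- All 60 invited, 71% consent to follow-up, 71% respond: 60 × 0.71 × 0.71 = 30.2.
- The 68% eligibility and 80% receipt thresholds also just met: 60 × 0.68 × 0.80 × 0.71 × 0.71 = 16.5.

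| Assumed paper share | Forms out of 30.2 | Forms out of 16.5 |
|---|---|---|
| 10% | 3.0 | 1.6 |
| 30% | 9.1 | 4.9 |
| 50% | 15.1 | 8.2 |

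These count forms that RCs could read. They do not measure bias.

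**The case against.** The strongest reply is that the assurance belongs to the electronic route. It sits between the sentence on people who can complete an electronic survey and the sentences on the central email. The paper route starts a new paragraph with its own procedure, and the assurance is not repeated there. On that reading nothing conflicts. The reading is possible, but the wording does not impose it. It would also leave paper respondents with only the general confidentiality statement while their ratings stay open to the staff who ran the encounter. The text needs reconciling either way.

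Several stronger readings are tempting, and the objection to each of them stands:

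- A reader might infer that completed forms come back unsealed. The unsealed envelope describes the hand-out; a respondent could seal it before return. The scanning step carries the point.
- A reader might infer that all 21 non-demographic items are biased. Step 4 shows otherwise: a form being visible does not mean that every answer on it is distorted.
- A reader might take 16–17 as the expected number of completed surveys. That treats minimum thresholds as expectations. It also depends on who counts as invited in the response-rate denominator.
- A reader might take courtesy bias as established. A paper respondent who believes the assurance has little reason to soften answers. The bias is a plausible inference, and the documents do not demonstrate it.

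The consequences are also limited: paper is a fallback, and the CUE-R 2 data are summarised descriptively in a single cohort, so no comparison or test is distorted.

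**Conclusion.** The point holds as an inconsistency to be corrected: as written, the assurance cannot be kept for paper respondents, because site RCs scan their completed forms. The conclusion rests on reading the assurance as unrestricted by mode, which is its plain wording. For electronic surveys it is not contradicted.

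The possible statistical effect is confined to paper CUE-R 2 answers, chiefly satisfaction, acceptability and confidence, and to the survey response rate if critical forms are withheld. Its size cannot be computed from the document. The eligible-encounter and infographic-receipt proportions, the sample size and the success thresholds are untouched. It should be fixed, but a fallback route in a descriptive pilot, with no demonstrated bias, does not justify treating it as critical.

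**What to change.** Have each paper respondent seal the completed form in an envelope that is either mailed directly to the SWAT research team or forwarded to it unopened by the site. Delete the step in which RCs scan and email completed surveys. Record survey mode for each response, so that readers can see how many came on paper. If the paper route cannot be changed, the minimum is to reword the assurance so that it is true for paper respondents.

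The cost is envelopes and postage, somewhat slower arrival of paper forms, and a minor ethics amendment.

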**Table 1 Tab1:**
[figure not shown]
Standard Protocol Items: Recommendations for Interventional Trials (SPIRIT) figure

Legend: This table summarizes participant activities for both phases of this study, which will take place over a 12-month period. *The first email follow-up will be sent to all patients/SDMs who consent to follow-up and will contain an electronic link to the CUE-R 2 questionnaire. +The second email follow-up will be sent to patients/SDMs who do not complete the CUE-R 2 1 week after the initial email was sent. Abbreviations: *CUE-R 2*, Consent Understanding Evaluation-Revised 2 Tool; *CRF*, case report form

### Sample size

We will use a sample of consecutive REMAP-CAP consent encounters at each of our study sites. Due to funding and study personnel constraints, we will recruit patients/SDMs for up to 6 months. Based on historical recruitment rates, we anticipate 2 patients per month, per site, for a total of 60 patients/SDMs. We conducted a sample size calculation using a confidence interval approach and expect our target sample size of 60 patients/SDMs to be sufficient to achieve our feasibility objectives [30]. We selected eligible consent encounters as our most important outcome, thus basing our calculation on a proportion of ≥ 68%, alpha = 0.1 and a margin of error of 10%, for a sample size of 60. We will seek feedback from all RCs consenting during this time. We anticipate 1–2 RCs per site for a total of 5–10 RCs. We will meet with RCs at each site before study implementation.

### Intervention

We will provide patients/SDMs with the infographic from phase 1 to augment the standard REMAP-CAP consent process. The standard consent process includes consent documents provided to the patient/SDM and an explanation/discussion of the study between the patient/SDM and study RCs. For consent encounters that occur in person, a paper copy of the infographic will be provided to the patient/SDM with the standard consent documents. For remote consent encounters (by telephone or videoconference), an electronic copy of the infographic will be provided with the standard consent documents.

### Outcomes

The primary outcome of this pilot study is feasibility. For patients/SDMs, this will include receipt of the infographic, consent to follow-up, and the completion of follow-up surveys. For RCs, this will include successful implementation of the infographic. We will collect additional data regarding the feasibility and acceptability of this intervention using patient-centered outcomes. We will collect data from both patients/SDMs and RCs who participate in the consent encounters.

#### Patients/SDMs

We will use a modified version of the Consent Understanding Evaluation-Revised tool (CUE-R) [31]. The CUE-R is a structured interview tool which was developed through a literature review and expert opinion, and validated through focus groups with research participants and community advisory board members, and later expanded to assess satisfaction with the consent process and consent documents [31, 32]. We modified the CUE-R to a self-administered survey, include both patients and SDMs as potential survey respondents, and fewer questions. Modifications were made through consensus among our multidisciplinary SWAT research team, including patients/SDMs, REMAP-CAP RCs, and investigators. We called our modified version of the CUE-R tool the “CUE-R 2” (Table 2). Participants who choose to complete an electronic survey will receive a unique survey link through LimeSurvey that will prevent duplicate responses. Both electronic and paper versions of the CUE-R 2 will conclude with five demographic questions including gender, age, race, highest level of education, and previous participation in medical research.

**Table 2 Tab2:** Phase 2 outcome measures, constructs, and questions

		**Question type (no. of questions)**		
	**Outcome**	**Likert style**	**Close-ended**	**Open-ended**
**CUE-R 2 (26 questions)**				
** Feasibility**	Consent mode & decision		2	
	Extent infographic was used	1		
	Ease of use of infographic	2		
	Acceptability of infographic	1		3
** Effectiveness**	Trial-related knowledge		4	
	Extent standard consent documents were used	1		
	Ease of use of consent documents	2		
	Satisfaction with information received	1	2	
	Desire for further information	1		
	Confidence in consent decision	1		
	Demographics		5	
**Research coordinator CRF (15 questions)**				
** Feasibility**	Consent mode & decision		3	
	Duration of consent encounter		1	
	Successful implementation of infographic		4	
	Ease of use of infographic	1		
** Effectiveness**	Satisfaction with consent encounter	1		
	Number & difficulty of questions asked	1	1	
	Perception of patient/SDM comprehension	1		
	Perception of patient/SDM satisfaction	1		
	Perception of patient/SDM confidence	1		

Legend: This table summarizes outcome measures for phase 2. The CUE-R 2 electronic survey will be completed by patients/SDMs who receive the consent infographic. The research coordinator (RC) CRF will be completed electronically by RCs who use the infographic during consent encounters with patients/SDMs. Abbreviations: *CUE-R 2*, Consent Understanding Evaluation-Revised 2 Tool; *CRF*, case report form

#### RCs

We will collect data using a modified version of a case report form (CRF) used in a SWAT of video-augmented consent for an ICU rehabilitation trial [33]. Outcomes are summarized in Table 2 and Fig. 2. RCs will be asked to complete an electronic CRF on LimeSurvey for each consent encounter within 24 h, to decrease the potential influence of recall bias [34].

**Fig. 2 Fig2:**
[figure not shown]
Flowchart of phase 2 study participants and feasibility outcomes. *n* represents number. Red text represents feasibility metrics. CUE-R 2, Consent Understanding Evaluation-Revised 2 Tool

### Data management

Raw data and analysis files will be password protected and stored on a password-protected computer. We will keep a copy of data files on the McMaster University secure network, and only SWAT research team members will have access. Completed hard copy surveys will be stored in a locked filing cabinet in a locked office.

### Data analysis

Data will be analyzed using Stata (v. 15.0, StataCorp LP, College Station, TX, USA). For the CUE-R 2, we will analyze demographic and survey response data using descriptive statistics, including using counts, frequencies, and means (standard deviations) or medians (1st, 3rd quartiles) for Likert-style questions or if data are skewed. We will narratively summarize text data from open-ended questions. We will calculate survey response rate as the proportion of completed surveys compared to the number of patients/SDMs who are invited to participate [35]. We will also calculate the proportion of partially completed and fully completed surveys. We will analyze RC CRFs using descriptive statistics. We will assess success of implementation using three metrics: (1) eligible consent encounters (proportion of patients/SDMs identified to receive the infographic compared to total number of REMAP-CAP consent encounters during the study period ≥ 68%, based on potentially eligible consent encounters in an ICU-based SWAT of video consent [33]); (2) receipt of infographic (number of patients/SDMs who received the infographic as a proportion of eligible consent encounters, ≥ 80%, suggested as the lower limit for high intervention fidelity [36]); and (3) feasibility of data collection will be assessed by consent rate for follow-up [≥ 71%, based on a systematic review of consent rates for trials in the ICU (lower limit of 95% confidence interval for median consent rate) [37]] and the survey response rate (≥ 71, based on the survey response rate in an ICU-based SWAT of video consent [33]).

### Confidentiality

Emails will be stored separately from survey responses; a master log containing email information will be created for this purpose. All email communications will be through a generic study email, hosted on the McMaster University secure domain.

### Remuneration

After survey completion, we will provide survey respondents with a CAD $5 gift card. This is intended to recognize participants’ time and important contributions; however, we do not believe this is enough to coerce study participation. Compensation will not be revoked in the case of incomplete survey responses. We will also provide RCs at our pilot sites with a CAD $50 gift card in appreciation of their time and expertise in implementing our study protocol.

### Dissemination policy

We will disseminate results through a peer-reviewed publication, national and international presentations.

### Mixed-methods integration

Data integration will occur at two points in this study [21]. The first, primary point of integration is before phase 2, where qualitative focus-group data will be used to develop a consent infographic that will be tested quantitatively. Once phase 2 is complete, we will integrate the results from both phases to understand if and how the quantitative results build upon the qualitatively informed infographic. Transcripts from phase 1 will be used during this point of integration. This second point of integration will inform future evaluation of the infographic in a future randomized trial across REMAP-CAP sites. Lastly, we will use investigator triangulation (multiple researchers involved in data collection and analysis) and methodologic triangulation (multiple methods of data collection) to improve the validity of our results [38].

## Discussion

### Strengths and limitations

Our study is patient-led, patient-oriented, and patient-centric. We partnered with patients and SDMs with lived ICU research consent experience who ideated this project. They are members of our research team, and their engagement will ensure the relevance of our work for patients and SDMs. Our multi-site pilot study will identify feasibility challenges through detailed data collection and feedback from stakeholders. These data will be critical to future implementation and evaluation of the consent infographic.

Representation of the 36 heterogeneous Canadian REMAP-CAP sites and contexts was a challenge. We chose to pilot the infographic at five sites in Southern Ontario, because of their high historical recruitment rates for REMAP-CAP. We will pilot the infographic in English, limiting our representation of non-English-speaking patients and SDMs who utilize the Canadian healthcare system. However, in our future evaluation study, we will include additional sites (nationally and internationally) and will consider translation to additional languages.

### Significance

Feasibility data are essential to optimize implementation and evaluation of a new intervention. Results from this study will be used to scale up and evaluate our consent infographic at additional REMAP-CAP sites. If successful, an infographic to support the traditional consent model could be more broadly tested. Use of a co-designed infographic during the consent process may benefit all stakeholders. Patients and SDMs may better comprehend trial information and increase their knowledge of REMAP-CAP, while RCs may experience improved patient/SDM understanding. In combination, these improvements may benefit the study through increased RC satisfaction, increase patient/SDM satisfaction, and well-informed consent decisions.

## Data Availability

Not applicable

## Abbreviations

ICU: Intensive care unit
SDM: Substitute decision-maker
REMAP CAP: Randomized, embedded, multifactorial, adaptive platform trial for community-acquired pneumonia
CAPTIC: Canadian Adaptive Platform Trial in Intensive Care
PFP: CAPTIC patient/family partners
HCD: Human-centered design
RC: Research coordinator
SPIRIT: Standard Protocol Items: Recommendations for Interventional Trials
SWAT: Study within a trial
CUE-R: Consent Understanding Evaluation-Revised tool
CRF: Case report form
